**Fig. 2 Fig2:**
[figure not shown]
UPlusE intervention flow

Parents in the control group (CG) receive the same questionnaires; however, patients of the CG get their results only at the U6 checkup at the child’s age of 10–12 months (end of the observation period), with regular care provided until then.

### Criteria for discontinuing or modifying allocated interventions {11b}

The intervention does not involve invasive or burdensome procedures. The control group receives usual care. Here, neither the doctor nor the patients receive the screening results before U6. If clinical indications of a mental disorder, psychosocial stress, or impaired bonding are identified during clinical assessments or at the final evaluation at U6, the individuals are also encouraged to seek support. In the control group, the same questionnaires are used at all measurement points like in the intervention group to obtain differentiated evaluation results.

If the question about suicidality is answered positively in the EPDS (the thought of harming myself has occurred to me: yes, quite often, or sometimes), the physician receives a note and will give a treatment recommendation immediately—regardless of control—or intervention group. The same procedure applies, when a specific question indicates a risk to the child’s well-being: the treating physician can immediately respond, initiate a conversation with the parents, and take appropriate measures. In general, both the control and intervention groups are shown general information in the app about whom to contact during acute crises and suicidal thoughts, regardless of questionnaire results.

The risk of stigma due to this screening appears to be very low. On the contrary, the training of doctors, systematic screening of all parents, and the information about the apps are intended to counteract stigma. The KID-PROTEKT screening questionnaire was developed in collaboration with affected individuals, and the wording was chosen to avoid stigmatization. Individuals retain their autonomy at all times regarding whether data is shared within the network and whether they accept assistance or seek psychological treatments.

The UPlusE intervention is purely advisory in nature and does not involve invasive elements. Therefore, the formulation of termination criteria or criteria for discontinuing or modifying allocated interventions is not necessary. Nevertheless, every patient who wishes to quit the study can do so at any time.

### Strategies to improve adherence to interventions {11c}

UPlusE is a module of a special care program (BKK Starke Kids) offered by the participating health insurance companies (58 BKKs). When patients in Germany choose to participate in a special care program, they receive clear advantages in their healthcare but also enter into legally binding obligations. With UPlusE, the obligation entails committing to their treating doctor for the duration of the care and filling out the questionnaires in the practice apps. Since the UPlusE study evaluates the UPlusE healthcare provision form, the study and the healthcare provision program are inseparable. Therefore, the legal regulations for the special care program apply here at least for BKK-insured individuals. Participants who no longer wish to take part in the study after more than 2 weeks must terminate their participation in the special care program. Until then, the obligation to complete the questionnaires remains. When it is time to fill out the questionnaires, participants will receive a push notification prompting them to do so. In case the questionnaire completion is forgotten or omitted, a reminder will be triggered.

### Relevant concomitant care permitted or prohibited during the trial {11d}

All participants will receive treatment as usual in addition to the study intervention. There are no treatments or interventions that would be prohibited during the study.

### Provisions for post-trial care {30}

UPlusE is a program for healthcare provision that is being investigated within the real healthcare setting with the aim of integrating it into regular care. Damages due to the intervention are not anticipated due to the non-invasive nature of the intervention. Therefore, we expect that compensation for any incurred damages will not be necessary.

### Outcomes {12}

The primary and secondary endpoints, as well as the parameters of the process evaluation, are presented in Table 1 along with the time points for assessment and measurement methods.

**Table 1 Tab1:** Primary and secondary outcomes UPlusE evaluation

Primary endpoint	Measurement	Time points	Methods
Utilization of services from mental health practitioners/"Early Prevention"	Project-specific questionnaire	From inclusion to U6 checkup	Apps ‘My Paediatric Practice’, ‘My Gynaecology Practice’, all participating parents
Secondary endpoints			
Depression/severity of depression	EPDS (Edinburgh Postnatal Depression Scale)	From inclusion to U6 checkup	Apps (as above), all participating parents
Parent–child bonding	PBQ (Postpartum Bonding Questionnaire)	From inclusion to U6 checkup (child's age of 10–12 months)	Apps (as above), all participating parents
Psychosocial burden	KID-PROTEKT questionnaire	From inclusion to U6 checkup (child’s age of 10–12 months)	Apps (as above), all participating parents
Child regulation	Extended SFS questionnaire	From inclusion to U6 checkup (child’s age of 10–12 months)	Apps (as above), all participating parents
Stigmatization	Project-specific questionnaire	Inclusion and U6 checkup (child’s age of 10–12 months)	Apps (as above), all participating parents
Process evaluation, participant acceptance/satisfaction	Project-specific questionnaire	At U6 checkup (child’s age of 10–12 months)	Apps (as above), parents in the intervention group
Process evaluation, acceptance/satisfaction of participating practices	Project-specific questionnaire	After completion of implementation phase (months 33–35)	Apps (as above), all participating gynaecological and paediatric practices
Process evaluation, acceptance/satisfaction of mental health practitioners/ ‘Early Prevention’	Project-specific questionnaire	After completion of implementation phase (months 33–35)	All involved mental health practitioners/ ‘Early Prevention’ services
Utilization of services in the healthcare system	Analysis of data from the participating health insurance funds	After completion of implementation phase	Data from all participating parents and children
Healthcare system costs in the first year after childbirth	Analysis of data from the participating health insurance funds	After completion of implementation phase	Data from all participating parents and children

All questionnaires for all data assessments time points will be made available in the apps ‘My Gynaecology Practice’ and ‘My Paediatric Practice’, and parents will be prompted to fill them out a few days before each U-checkup appointment.

### Participant timeline {13}

Depending on entry point (enrolment into the study during pregnancy or at U3-, U4- or U5-checkup) and potential screening point at which a participant in the intervention group screens positive and is motivated for treatment, the duration of the intervention with follow-up observation varies between 6 and 15 months. The intervention is carried out up the U6-checkup (at child’s age 10 to 12 months). The participant timeline is depicted in Fig. 3.

**Fig. 3 Fig3:**
[figure not shown]
UPlusE schedule of enrolment, interventions, and assessments (SPIRIT)

### Sample size {14}

The proportion of all parents who avail themselves of any mental health services is based on the available figures. (18% [22], health insurance data: 10–12%) and is assumed to be 15% in the following. The assumption is that through the intervention, the proportion of affected parents using mental health services can be increased to at least 25% in the intervention group. With *α* < 0.05 and a power of 0.80, a sample size of 500 subjects is therefore required. The cluster-randomized controlled design must be considered when calculating the required number of participants. The design effect due to cluster randomization is estimated at 1.725 (intra-cluster correlation (ICC): 0.15; number of patients/practices: 2.5). With a dropout rate of 20%, the number of required positively screened subjects is (500 × 1.725) / 0.80 = 1078. Given a known prevalence of peripartum depression of 10–15% as the condition that is in our focus, a total of 10,000 parents (5000 each in the intervention and control groups) must be screened and included (Fig. 3).

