## Introduction

### Background and rationale {6a}

A good start in life can be significantly compromised by a parent’s mental illness. Perinatal depression has a prevalence of 10–15% among mothers [1] and approximately 5% among fathers [2]. Psychosocial stressors (including depression) are reported by 30% of parents [3]. The prevalence of suicidal thoughts during pregnancy and postpartum ranges from 5 to 14% [4]. Suicide is one of the leading causes of death among mothers in the first year after childbirth [4]. However, significantly fewer individuals affected by a mental illness (like for example depression and anxiety disorders as the most common conditions) seek treatment during the perinatal period compared to other life phases [5]. Left unrecognized and untreated, both conditions can have negative long-term consequences for the family’s health and lead to high subsequent costs [6–8]. These illnesses often become chronic [9], resulting in impairments in sensitive caregiving for the child, attachment disorders, child regulatory problems, and, in the worst case, emotional neglect and abuse [10–12]. Early treatment of depression reduces individual suffering [1], enhances parenting skills [13], and reduces healthcare system costs [14–17]. Nevertheless, only a fraction of affected patients are diagnosed and treated early; due to lack of awareness and stigma, there is still a pronounced underdiagnosis and undertreatment [5, 18]. Gynaecologists and paediatricians regularly encounter individuals in this phase of life but frequently fail to recognize their psychological burdens [18]. For instance, there are highly functional affected individuals who appear capable and healthy, even though they are severely ill. Without a screening in routine care in these cases, mental illnesses often go unnoticed—with all the aforementioned risks. To reliably and promptly identify mothers and fathers with perinatal mental illnesses screening by gynaecologists and paediatricians is meaningful, feasible, and urgently needed [4, 14, 19–21]. So far, there are no general, systematic, and standardized early detection programs in Germany, and timely, low-threshold, and tailored provision of support is not organized. While the current guidelines for children and maternity care of the German Federal Joint Committee* (Kinder- und Mutterschafts-Richtlinien des* Gemeinsamen Bundesausschusses (G-BA)) partially consider the need to recognize psychosocial burdens, these risk factors are only identified in individual cases, as binding and feasible standards for required assessment are lacking so far. Hence, the identification of mental illnesses, such as depression, in pregnant women and parents is not yet a part of routine care. This aspect will be addressed by the G-BA-funded project “UPlusE (U-Untersuchung für Kinder PLUS Eltern beim Pädiater zur Förderung der kindlichen Entwicklung mit Impuls aus frauenärztlicher Schwangerenvorsorge”—Paediatric Check-up for Children PLUS Parents at the Paediatrician to Promote Child Development with Input from Gynaecological Prenatal Care). Within UPlusE, a systematic and very low-threshold screening for peripartum/postnatal depression or high psychosocial stress in (A) pregnant women during the third trimester by their treating gynaecologists and in (B) parents during paediatric checkups (so called U-checkups) for their children (up to U6-checkup at age of 10–12 months) by their treating paediatricians will be conducted throughout Germany. In the case of a positive screening result, the affected parents will be referred by their respective doctors for appropriate support (including psychiatry, psychotherapy, and psychosomatics treatments, hereafter referred to as “mental health specialists”) and/or to “early prevention” and family support programs (including early prevention services *Frühe Hilfen*, *pro familia*, and family and parenting counselling centres, pregnancy counselling centre, child protection coordination centres as well peer support groups).

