
## Objectives {7}

The overall goal of UPlusE is to increase the utilization of treatment and counselling services for mothers and fathers experiencing perinatal depression, psychosocial distress, or impaired bonding preceded by a low-threshold screening for these conditions. Within UPlusE, the term psychosocial stress encompasses both psychosocial stress and impaired bonding. The main research question of the UPlusE project is: can the utilization of any support services by parents with psychological or psychosocial issues be improved through the low-threshold intervention? The working hypothesis is: there is a significantly higher utilization of support services in the intervention group between enrolment in the project and the U6 checkup (child’s age of 10–12 months) compared to the control group.

Additional secondary research questions:For parents positively screened for peripartum depression or psychosocial distress (in the following meant as psychosocial distress and impaired bonding):aWhat mental health services are utilized? What is the proportion of medication-based therapies? How quickly do they receive treatment?bHow frequently do various forms of child regulatory problems occur in this group?cDo child regulatory problems occur with varying frequency in families with different stress profiles (mental illness/psychosocial burdens)?

Sensitivity analyses will investigate the following questions:iv.Is the proportion of parents experiencing an improvement in depressive symptom severity higher when utilizing mental health services?v.Is the proportion of parents with an unaffected parent–child relationship higher when utilizing mental health services?vi.Do child regulatory problems occur less frequently in parents utilizing mental health services?

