‘quite often’, ‘sometimes’, ‘rarely’, and ‘never’) [27].5.Questionnaire on Crying, Feeding, and Sleeping (SFS):For measuring infant regulatory disorders, the extended SFS questionnaire will be used, comprising 37 items about infant crying, sleeping, and eating behaviour [28]. Total mean scores above 1.84 (crying and sleeping) or above 1.27 (feeding scale) indicate regulatory problems. Six items based on DC: 0–5 (classification system for the diagnosis of mental disorders in infants, toddlers, and preschool children) will be used for further differentiation and clinical classification of symptoms related to excessive crying, sleep disorders, and early childhood feeding disorders.6.Questionnaire on treatment/counselling utilization:Utilization of treatment for mental health issues and counselling for psycho-social stress and parent-child bonding issues will be systematically captured via a project-specific questionnaire in the practice apps ‘My Gynaecology Practice’ and ‘My Paediatric Practice’ through self-report by the participants. The questionnaire assesses information about whether treatment/counselling has been sought. If utilization has occurred since the previous assessment, details such as the institution visited (pregnancy counselling centre, child protection coordination centres, ‘Early Prevention’ services, specialized outpatient clinic, psychiatrist/psychosomatics/psychotherapist, general practitioner, other), the motivating factor, and the referrer will be collected. As of our knowledge, specifically fitting standardized, validated, and publicly published questionnaires for this purpose are currently not available.7.Process analysis questionnaireTo identify technical and organizational barriers as well as facilitating factors for the implementation of the care model, a process evaluation will be conducted. This involves surveying all participating practices, mental health practitioners, and counselling services. Except for mental health practitioners and ‘Early Prevention’, the survey will be conducted using project-specific questionnaires via the practice apps ‘My Gynaecology Practice’ or ‘My Paediatric Practice’. Mental health practitioners and ‘Early Prevention’ services cannot be reached through the practice apps: for the process evaluation, these recipients will be invited to participate in the survey via email by the responsible contact persons from the study team. The survey will use a digital form. The questionnaires for process evaluation will be designed by the Institute for Community Medicine, University Medicine Greifswald, and will cover aspects such as:The number of participating practices, mental health practitioners, and ‘Early Prevention’ services.Their reasons for participation.The feasibility of implementing the intervention in their respective settings.Acceptance of the intervention.Perceived technical and/or organizational barriers or gaps in the implementation of the intervention.Benefits perceived by the involved practices, mental health practitioners, and ‘Early Prevention’ services due to the intervention,Factors promoting the implementation of the care model.

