## Statistical methods

### Statistical methods for primary and secondary outcomes {20a}

The intervention in UPlusE will be scientifically evaluated using a multidimensional approach and various methods (multilevel analyses, process analyses, secondary data analysis) that, in combination, allow for a comprehensive assessment of different aspects of the project.

All data analyses will be conducted using pseudonymized data. After the observation period (U6), the primary and secondary endpoints for parents with psychological and psychosocial issues will be analysed in a group comparison (comparison between the intervention and the control group). Multilevel analyses will be conducted based on the intention-to-treat principle.

Additionally, the trajectory of values and the utilization of services for parents without psychological and psychosocial issues at the time of project inclusion (clinical evaluation) will be descriptively analysed. Quantitative parameters will be analysed using multilevel analyses to correct for cluster randomization. In the case of structural inequality between the intervention and control groups, relevant parameters (such as age, gender, number of pregnancies and births, partnership, socioeconomics—education, occupation, financial situation, severity of depression) will be adjusted for. All tests will be two-tailed with a significance level of alpha = 0.05.

In the analysis, a descriptive evaluation (e.g. symptom severity, child symptoms, service utilization) will be conducted for the group of parents who were positively screened. At the time of U6, a comparison between the intervention and control groups will be performed (e.g. symptom severity, parent–child bonding, child symptoms). Furthermore, across groups, psychosocial stress, depressive symptoms, stigma, and service utilization will be assessed.

The data from the process analysis questionnaires will be analysed descriptively and inferentially.

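### The stated 80% power is calculated for mental-health-service use, with numbers scaled by depression prevalence, and so does not refer to the declared primary comparison

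*Protocol article*

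**What the plan says.** **Sample size {14}.** The control rate is introduced with "The proportion of all parents who avail themselves of any mental health services is based on the available figures" and set at 15%. The target is that "the proportion of affected parents using mental health services can be increased to at least 25% in the intervention group". With 80% power this gives 500 subjects. A design effect of 1.725 and 20% dropout raise that to 1,078 positively screened parents. The step to 10,000 screened uses the prevalence of peripartum depression, 10–15%.

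**Objectives {7}.** The main research question is: "can the utilization of any support services by parents with psychological or psychosocial issues be improved through the low-threshold intervention". The same section counts impaired bonding as part of psychosocial stress.

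**Outcomes {12}, Table 1.** The primary endpoint is "Utilization of services from mental health practitioners" or Early Prevention.

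**Statistical methods {20a}.** After U6, "the primary and secondary endpoints for parents with psychological and psychosocial issues will be analysed in a group comparison". Trial design {8} likewise says that the relevant comparison is between positively screened participants of the two arms.

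**Abstract and Intervention description {11a}.** A result is positive at EPDS ≥ 10, KID-PROTEKT ≥ 1 or PBQ-1 ≥ 12. Parents with EPDS below 10 who are positive on one of the other two instruments are pointed to Early Prevention and counselling.

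**Background {6a}.** "Psychosocial stressors (including depression) are reported by 30% of parents".

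**The concern.** Endpoint and population both change between the power calculation and the comparison it is meant to support.

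- **Endpoint.** The calculation counts mental health services only. Background {6a} keeps mental health specialists (psychiatry, psychotherapy, psychosomatics) apart from Early Prevention and family support, so the narrower term is not plainly shorthand for the Table 1 endpoint. For parents positive only on KID-PROTEKT or PBQ-1, the contact that the intervention is meant to produce counts in Table 1 but not in the sample size.
- **Population.** The count of positives comes from depression prevalence, whereas positivity is defined on three instruments. In addition, the 15% is stated for all parents and the 25% for affected parents, so the two rates do not describe one group.

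At stake is what the trial can claim. If the control rate, the expected gain, the number of positives and the number per practice all differ from those used, 80% is not the power of the confirmatory test, and nobody can say from the protocol what that power is.

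**Working it through.** **1. Reproduce the plan's figure.** Inputs from Sample size {14}: 15% v 25%, power 0.80, 1:1. Two-sidedness comes from Statistical methods {20a}: "All tests will be two-tailed with a significance level of alpha = 0.05". With pooled variance under the null and no continuity correction,

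n per arm = [1.96·√(2·0.20·0.80) + 0.842·√(0.15·0.85 + 0.25·0.75)]² / 0.10² = 250, so 500 in total.

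Inflation: 500 × 1.725 / 0.80 = 1,078. Share of those screened: 1,078 / 10,000 = 10.8%, within 10–15%. The 80% is therefore correct for 15% v 25% in mental-health-service use, taking 1.725 as given.

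**2. Set the two comparisons side by side.**

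| | Sample size {14} | Declared primary comparison |
|---|---|---|
| Endpoint | Mental health services | Any support service, or mental health practitioner/Early Prevention |
| Population | Control rate: all parents; target: affected parents | Positive on EPDS, KID-PROTEKT or PBQ-1 |
| Prevalence | 10–15% (depression) | Not given; 30% is cited for psychosocial stressors including depression |
| Control and target rates | 15%, 25% | Not given |

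**3. Range of power for the declared comparison.** The rates below are assumptions, since the protocol gives none.

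*Case A: 1,078 positives at the stated design effect.* Effective total = 1,078 × 0.80 / 1.725 = 500, or 250 per arm.

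*Case B: 30% positive (assumption).* Positives = 10,000 × 0.30 = 3,000. Practices implied by the protocol = 1,078 / 2.5 ≈ 431. Positives per practice = 3,000 / 431 ≈ 7.0. Design effect = 1 + (6.96 − 1) × 0.15 ≈ 1.89. Effective total = 3,000 × 0.80 / 1.894 ≈ 1,267, or about 634 per arm.

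Power = Φ{[(p₂ − p₁)·√n − 1.96·√(2p̄(1 − p̄))] / √(p₁(1 − p₁) + p₂(1 − p₂))}, with n per arm and p̄ the mean of the two rates:

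| Control v intervention | Case A | Case B |
|---|---|---|
| 15% v 25% | 0.80 | 0.99 |
| 30% v 40% | 0.65 | 0.96 |
| 15% v 20% | 0.31 | 0.65 |
| 30% v 35% | 0.22 | 0.48 |

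More positives raise power. A control rate nearer 50%, a smaller gain and more positives per practice lower it. The net direction is open.

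**4. Stability of the cluster-size input.** With ICC 0.15 and 2.5 per practice the design effect is 1 + 1.5 × 0.15 = 1.225, not 1.725. A value of 1.725 at ICC 0.15 needs 1 + 0.725 / 0.15 ≈ 5.8 per practice. Scaling from 5.8 instead of 2.5 gives 5.83 × 3,000 / 1,078 ≈ 16 positives per practice and a design effect of about 3.3. Power for 15% v 25% is then about 0.92. Case B is thus an illustration and not an estimate.

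**The case against.** **The wording is less narrow than it looks.** The sample size section speaks of affected parents and of positively screened subjects. Depression enters through the prevalence step, where the protocol calls it the condition in focus. This is fair: the section does not literally restrict itself to depressed parents. But the prevalence step is what turns 1,078 into 10,000, and the endpoint there is still mental health services.

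**The objective and Table 1 nearly coincide.** Read with the two referral groups in Background {6a}, any support service and practitioner/Early Prevention use overlap heavily. The questionnaire's further answer options ("specialized outpatient clinic, psychiatrist/psychosomatics/psychotherapist, general practitioner, other") are response categories, and coding them can be left to an analysis plan. That largely stands, so the gap that matters is between both of these and the sample size section.

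**Depression prevalence is the cautious choice.** A wider definition of positive yields more than 1,078 cases from 10,000. This is right for case numbers alone. It does not settle the power, which also depends on rates and clustering.

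**The 30% is not the positivity rate.** It is a figure for psychosocial stressors, not for being positive on any of three instruments at these cut-offs, and not cumulative over repeated screening. This stands, and 30% is used here only as an assumption.

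**Stronger readings that the documents do not support.** A reader might infer that the effect is diluted to about a third, because parents positive only on KID-PROTEKT or PBQ-1 are not sent to mental health specialists, and that the trial is therefore underpowered. But Early Prevention contacts count in Table 1, so that referral is a primary-endpoint event. A reader might also infer that the endpoint can be picked after the data are seen. Table 1 names one primary endpoint and the analysis plan is not at hand, so that would be speculation.

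**Conclusion.** The point holds as a mismatch of endpoint and population in the current text. The 80% power belongs to a 15% v 25% contrast in mental-health-service use, scaled by depression prevalence, and not to the declared primary comparison.

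Its effect on power is undetermined. In the scenarios examined, power runs from 0.22 (1,078 positives, 30% v 35%) to 0.99 (3,000 positives, 15% v 25%), and a 10-point gain with 3,000 positives is well covered. These values rest on assumed rates, an assumed 30% positivity, the stated ICC and dropout, and a cluster size that the protocol's own design effect contradicts. They show that the power is unknown, not that it is low.

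The correction matters because the trial justifies its 10,000 parents by this figure.

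**What to change.** Keep the Table 1 endpoint (mental health practitioner or Early Prevention use) and the population positive on any of the three instruments as primary. Then:

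1. Align Objectives {7}, Outcomes {12}, Sample size {14} and Statistical methods {20a} to that pair.
2. Recompute the sample size section with control rate, target rate, prevalence and positives per practice for exactly that endpoint and population. Give both rates for the same group of parents, and reconcile the design effect with its inputs.
3. Restate the power that 10,000 parents deliver, over a range of control rates if no good source exists.
4. Report mental-health-service use in EPDS-positive parents as a prespecified secondary analysis.

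Narrowing the primary population to EPDS ≥ 10 at enrolment is not a good alternative. It would replace the stated research question and drop parents who turn positive later. At the pilot's roughly 10% prevalence it would yield about 1,000 cases, below the 1,078 required.

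The cost is wording and a recalculation, with no extra patients. The downside is that the restated power may differ from 80%.
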